## Abstract

**Study design::**

This is a prospective, single-center, randomized controlled trial. Patients with acute ischemic stroke caused by atherosclerotic carotid artery occlusion confirmed by imaging (computed tomography/magnetic resonance angiography/digital subtraction angiography) will be randomly divided into the study and control groups, with 101 patients in each group. The study group will undergo surgery according to the ECASES system and the control group will undergo surgery according to the operator’s experience. The postoperative outcomes of the 2 groups will be compared.

**Study outcomes::**

Primary outcome: Neurological functional status (modified Rankin Scale and National Institutes of Health Stroke Scale scores) of patients 90 days postoperatively. Secondary outcomes: neurological function changes, hemorrhage events, cerebral edema, postoperative modified treatment in cerebral infarction grade, new cerebral infarction, and reocclusion of responsible vessels.

**Discussion::**

Currently, no prospective controlled data exist regarding the efficacy and safety of carotid stenting in the acute phase. Previously, we had developed an ECASES stent placement system for acute carotid artery occlusion. The present study will evaluate the efficacy and safety of ECASES in a randomized, double-blind prospective study and clarify its guiding significance in acute atherosclerotic carotid artery occlusion surgery.

## 1. Introduction

Large-vessel occlusion can cause ischemic stroke and is closely associated with poor prognosis. Intravenous thrombolysis is inefficient for recanalization of large-vessel occlusion, and intravascular intervention has become the standard treatment for acute stroke with large-vessel occlusion.^[1–3]^ Despite the rapid development of surgical techniques and materials and significant improvements in the surgical recuperation rate, many difficulties and controversies remain regarding some disease subtypes, whether in surgical techniques or strategies and are worthy of further study.

Atherosclerotic acute carotid occlusion is a specific type of large vessel, occlusive acute stroke. Its etiology is based on atherosclerotic stenosis at the beginning of the internal carotid artery and acute occlusion of the carotid artery due to hemodynamic or other causes, which is often accompanied by embolization of large intracranial vessels (tandem occlusion), resulting in acute cerebral infarction. The current surgical treatment for acute carotid occlusion in atherosclerosis is controversial at both the technical and strategic levels.^[4]^ One main controversy is whether to place a stent in the carotid artery immediately after opening the occluded vessel.^[5,6]^ The advantage of stent placement is that it guarantees patency of the vessel and reduces the risk of postoperative vessel reocclusion; however, it may increase the risk of intracranial hemorrhage owing to the application of antiplatelet agents and excessive perfusion. Without stenting, the risk of intracranial hemorrhage may be reduced; however, the risk of postoperative vessel reocclusion increases. The conclusions of the available studies are inconsistent. Some studies have shown results favoring simultaneous stent placement, but others have shown the opposite, and others have concluded that stent placement has no effect on patient prognosis.^[7,8]^

We believe that assessment and decision making should be individualized and objective for each patient and cannot be generalized. In our previous work, we summarized a decision evaluation system, Emergent Carotid Artery Stent placement decision Evaluation System (ECASES), for stent placement decisions in atherosclerotic acute carotid artery occlusion. The system is divided into 3 parts: bleeding risk score, ischemia risk score, and an individualized decision-making system that can specifically and quantitatively assess a patient’s risk of intracranial hemorrhage and ischemia and make individualized treatment recommendations.

Therefore, this study aimed to further evaluate the efficacy and safety of ECASES through a randomized, double-blind, prospective controlled study to clarify its guiding significance in acute atherosclerotic carotid artery occlusion surgery.

## 2. Methods

### 2.1. Study design

This is a prospective controlled study with a randomized, double-blind design, in which subjects will be randomized into 2 groups: the study group will undergo surgery according to the ECASES system and the control group will undergo surgery according to the operator’s experience. The postoperative results of the 2 groups will be then compared. This study was registered in the Chinese Clinical Trial Registry (Identifier: ChiCTR2200055890) and will be conducted in accordance with the Declaration of Helsinki and Good Clinical Practice guidelines.

### 2.2. Study population and preoperative evaluation

The study population will include patients with acute ischemic stroke caused by atherosclerotic carotid occlusion and confirmed by imaging (computed tomography angiography (CTA)/magnetic resonance angiography (MRA)/digital subtraction angiography (DSA)) attending Tianjin Huanhu Hospital, and 202 patients are planned to be enrolled: 101 patients in the study group and 101 patients in the control group.

1)Inclusion criteria.•Age 18–80 years old, regardless of sex.•Preoperative National Institutes of Health Stroke Scale (NIHSS) score ≥ 6.•An Alberta Stroke Program Early Computed Tomography Score (ASPECTS) ≥ 6 based on magnetic resonance imaging diffusion-weighted imaging (MRI-DWI) sequences.•The time from onset to the expected start of endovascular treatment is ≤ 24 hours, with patients between 6 and 16 hours meeting the inclusion criteria for the DAWN study and the DEFUSE 3 study, and patients between 16 and 24 hours meeting the inclusion criteria for the DAWN study.•Pre-stroke modified Rankin Scale (mRS) score of 0–1.•Life expectancy ≥ 2 years.•Patients and their families agree to the endovascular treatment and study protocol and sign an informed consent form.2)Exclusion criteria.•Patients with combined intracranial hemorrhage confirmed by CT or MRI.•Patients with a combination of severe renal insufficiency (creatinine level > 264 µmol/L), respiratory and circulatory instability, severe coagulation dysfunction (international normalized ratio > 3.0, or partial thromboplastin time more than 3 times the normal value), and other contraindications to interventional procedures.•Patients with preexisting neurological(pre-stroke mRS score ≥ 2, stroke attack with epilepsy, combined with intracranial tumors) or psychiatric disorders could confound the results.•Uncontrollable hypertension is defined as a systolic blood pressure > 185 mm Hg and diastolic blood pressure > 110 mm Hg.•Platelet count < 50,000/µL.•Blood glucose < 2.78 mmol/L or > 22.20 mmol/L.•Patients who cannot undergo cranial MRI.•Patients deemed unsuitable for study participation by other investigators.3)Exclusion and discontinuation criteria: Patients may withdraw at any stage of the study.•Voluntary withdrawal, where informed consent is withdrawn, and patients are free to withdraw from the study at any time without prejudice to subsequent treatment.•Missed patient visits.•Any safety reasons (adverse events) as perceived by investigators.•Other cases where researchers decide whether it is appropriate for patients to withdraw from the study.4)Preoperative evaluation.•General information: Age, sex, time of onset, past medical history, and stroke risk factors, including blood pressure, blood glucose, blood count, coagulation series, and electrocardiogram.•Neurological function assessment: NIHSS and mRS scores will be used as tools for neurological function evaluation and completed by senior physicians.•Imaging evaluation: All patients undergo preoperative cranial CT to exclude intracranial hemorrhage and massive cerebral infarction. All patients will undergo cranial MRI to clarify the diagnosis and extent of acute cerebral infarction and will then be scored based on MRI-DWI sequences with reference to the ASPECTS scoring system. The presence of large infarcts in the basal ganglia area (large infarcts: >2/3 of the basal ganglia area) will also be assessed. All the patients will undergo MRA, CTA, and/or DSA to confirm the presence of atherosclerotic carotid occlusion. In some patients (6–24 hours after onset), CT perfusion imaging or nuclear perfusion imaging will be performed to assess the semidark bands.

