### 2.8. Study outcomes

Primary outcome: Neurological functional status at 90 days postoperatively

Patient neurological functional status will be assessed by mRS and NIHSS scores.

Secondary outcomes.

Changes in neurological function are classified as improved (postoperative NIHSS score decrease ≥ 4 points compared with preoperative), worsened (postoperative NIHSS score increase ≥ 4 points compared with preoperative), or stable (postoperative NIHSS score change < 4 points).Hemorrhage events: For the classification of bleeding events, we refer to ECASS II.^[9]^ Hemorrhagic events were classified according to the clinical and CT criteria. Hemorrhagic infarction 1 (HI1) was defined as small petechiae along the margins of the infarct, and hemorrhagic infarction 2 (HI2) as confluent petechiae within the infarcted area but no space-occupying effect.

parenchymal hemorrhage (PH1) as blood clots in 30% or less of the infarcted area with some slight space-occupying effect, and parenchymal hemorrhage (PH2) as blood clots in more than 30% of the infarcted area with a substantial space-occupying effect. Symptomatic intracranial hemorrhage was defined as blood at any site in the brain on the CT scan (as assessed by the CT reading panel, independent of the assessment by the investigator), documentation by the investigator of clinical deterioration, adverse events indicating clinical worsening (e.g., drowsiness, increase of hemiparesis), or a decrease in the NIHSS score of 4 or more points.

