### 2.12. Statistical analysis methods

All data will be analyzed according to the intentionality analysis and will follow the protocol analysis statistics. Statistical descriptions will be used to compare the baseline information. The mean ± standard deviation or median (interquartile range) will be used to express the measurement data, and rates or percentages will be used for count data. For measurement data, a *t* test or Mann–Whitney *U* test will be used to detect differences between the groups. The Chi-squared test will be used to analyze the count data.

All data will be analyzed using SPSS 23.0 (IBM Corporation, Armonk, NY) software, and *P* < .05 (2-sided) will be considered a statistically significant difference.

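### The study-exit list does not separate stopping treatment from stopping follow-up, so it can lose day-90 outcomes that the intention-to-treat analysis needs

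*Protocol article*

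**What the plan says.** Item 3 of section 2.2 opens with "Exclusion and discontinuation criteria: Patients may withdraw at any stage of the study". Apart from the patient's own withdrawal of consent, it lists three grounds:

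- "Missed patient visits"
- "Any safety reasons (adverse events) as perceived by investigators"
- "Other cases where researchers decide whether it is appropriate for patients to withdraw from the study"

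The last ground speaks of leaving the study, not of leaving treatment. No ground says whether assessment continues afterwards.

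Section 2.12 states: "All data will be analyzed according to the intentionality analysis and will follow the protocol analysis statistics". This reads as intention-to-treat, apparently with a per-protocol analysis beside it. Section 2.8 gives "Primary outcome: Neurological functional status at 90 days postoperatively", scored by mRS and NIHSS. It also lists hemorrhage, edema, new infarction and reocclusion as secondary outcomes. Section 2.7 schedules neurological assessments on days 1, 7, 30 and 90.

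**The concern.** A patient who leaves the study before day 90 has no primary outcome. Two of the listed grounds are not neutral reasons for leaving.

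- **Adverse events.** Section 2.2 does not define the term, but serious bleeding or reocclusion after the procedure would ordinarily fall within it. Such events are outcomes of the trial and are likely to go with a poor day-90 score.
- **Missed visits.** A patient absent on day 7 or day 30 can still be scored on day 90. A missed visit is missing data at that visit and need not end participation.

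The third ground has no stated limit, so it can be applied to patients who are doing badly.

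If outcomes are lost in this way, analysing everyone as randomised requires imputing scores that could have been collected. In a noninferiority comparison, heavier loss of poor outcomes in the study arm favours a conclusion of noninferiority. Heavier loss in the control arm works against it.

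**Working it through.** **Inputs from section 2.11.** Good-outcome rate 51% in both arms (labelled 180 days; assumed here to apply at day 90); margin −10 points; one-sided α 0.025; 101 patients per arm; 5% loss, which is 0.05 × 202 = 10.1 patients. The 101 per arm serves here only as a head count. It does not follow from its stated inputs: the usual two-arm formula gives 393 per arm before loss and 414 after. That is a separate matter and does not affect the percentages below.

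**Assumptions, not in the documents.** A share f of poor-outcome patients in an arm has no day-90 score, no good-outcome patient is lost, and only observed scores are analysed.

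**Formula.** Observed good-outcome rate = p / (p + (1 − p)(1 − f)).

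With p = 0.51:

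- f = 0: 0.510
- f = 0.05: 0.51 / (0.51 + 0.4655) = 0.523
- f = 0.10: 0.51 / (0.51 + 0.441) = 0.536
- f = 0.15: 0.51 / (0.51 + 0.4165) = 0.550
- f = 0.20: 0.51 / (0.51 + 0.392) = 0.565

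| Removed, study v control | Observed rates | Shift in difference | Overall loss |
|---|---|---|---|
| 10% v 10% | 53.6% v 53.6% | 0 | 4.9% |
| 10% v 0% | 53.6% v 51.0% | +2.6 points | 2.5% |
| 15% v 5% | 55.0% v 52.3% | +2.8 points | 4.9% |
| 20% v 0% | 56.5% v 51.0% | +5.5 points | 4.9% |

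Overall loss is 0.49 × (sum of the two shares) / 2. For 15% v 5% this is 0.49 × 0.20 / 2 = 4.9%, or about 10 of 202 patients. Swapping the arms reverses the sign of the shift.

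**Effect on the noninferiority test.** Take true rates at the margin, 41% (study) v 51% (control). Use a normal approximation with unpooled variance and 101 randomised per arm, less those removed. The one-sided false-positive rate is the probability that a standard normal variable falls below (observed difference + 0.10)/SE − 1.96.

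- No removal: 2.5%.
- 10% removed in both arms: 43.6% v 53.6%, and the rate stays at about 2.5%.
- 10% removed in the study arm only: 43.6% v 51.0%, with 95.0 and 101 patients. SE = √(0.436 × 0.564/95.0 + 0.51 × 0.49/101) = 0.071, and the rate is 5.5%.
- 15% v 5%: 45.0% v 52.3%, and the rate is 5.6%.

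**Could loss be unequal?** Section 2.5 has both the ECASES assessor and the surgical team recommend a plan for every patient, and the decision maker passes on one of them. In the control group this is always the surgical team's own plan. Only in the study group can it differ, so a surgeon given a different plan can infer the arm. Complications may also differ between the plans. Neither point shows that imbalance will occur.

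**The case against.** The strongest reply is that nothing in the article drops withdrawn patients from the analysis or exempts them from day-90 assessment. The list opens permissively, section 2.12 commits to intention-to-treat, and section 2.7 schedules visits without exception. Scheduled imaging suggests that complications are meant to be followed and counted. Rules for missing outcomes may sit in a full protocol or SAP that is not shown. Much of this stands, and it rules out four stronger readings.

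- A reader might infer that section 2.2 flatly contradicts section 2.12, or that poor outcomes will be removed. Both are inferences. The text creates a risk because it does not say what follows discontinuation.
- A reader might infer that withdrawal after a one-time procedure has no treatment purpose. Section 2.5 defines the plans partly by antiplatelet treatment that continues after surgery, so a safety ground for stopping treatment can have a purpose. Stopping a drug still does not require ending follow-up.
- A reader might infer that losses will exceed the planned 5%. Nothing shows this: at 51% in both arms, the 15% v 5% case loses 4.9% overall.
- A reader might infer that losing poor outcomes is enough to hide harm. Equal removal raises both rates and leaves the difference essentially unchanged. Section 2.3 states that investigators are blinded throughout, which works against unequal discretionary removal, although section 2.5 leaves the gap described above.

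The appeal to unseen documents does not answer the core point. This is a printed rule of conduct, and a later analysis plan cannot recover scores that were never collected.

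**Conclusion.** The concern holds in a limited form. Section 2.2 states grounds for leaving the study that include missed visits, adverse events and open discretion, without separating treatment from follow-up. Applied before day 90, they can cost the primary outcome in patients with complications and weaken the analysis promised in section 2.12.

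The size is conditional. It runs from no shift with equal loss to +2.6 or +2.8 points with modest imbalance against the study arm, about a quarter of the 10-point margin. With all of roughly 10 losses being poor outcomes in the study arm, it reaches +5.5 points. The removal shares are assumptions, and the direction would reverse if the control arm lost more. The point should be corrected before follow-up proceeds, but it is not evidence that the trial's comparison is already biased.

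**What to change.** Reword item 3 of section 2.2 so that discontinuing treatment and ending follow-up are separate, and align it with section 2.12:

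- Follow-up ends only when the patient withdraws consent to it.
- Patients with missed visits, adverse events or discontinued treatment stay in follow-up, and day-90 mRS is sought for them, by telephone if needed.
- All randomised patients are analysed in the group to which they were randomised.

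Any rule on stopping treatment for safety is left as it is. The planned sample size is not affected by this change. The cost is protocol wording and telephone contacts for a few patients.

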
### 2.3. Randomized grouping and blinding method

Randomized grouping method: Pass software will be used to randomize the study subjects into the study and control groups. The study subjects will be numbered, and random numbers will be generated using the pass software functions Transform-Compute (calculate new variables) - Rv.Uniform (uniformly distributed random number function). Transform-Rank Cases will be applied to generate a random number order.Blinding: The study will be double-blind, blinded to the patient and investigator, and neither the patients nor investigators will know the subject grouping throughout treatment and follow-up. The randomization grouping results will be maintained by a dedicated person (stenting protocol selection decision maker), who is a nontreatment/non-follow-up participant who is aware of the patient’s grouping assignment (study or control group) and maintains patient and investigator confidentiality.

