### 2.5. Treatment plan recommendation and determination

Three surgical options are currently available. Stent placement + immediate normal application of antiplatelet drugs; Stent placement + delayed application of antiplatelet drugs; and no stent placement. “Immediate normal antiplatelet medication” refers to an intravenous tirofiban loading dose before stent placement and continuous intravenous pumping (calculated by kilogram of body weight according to the instructions) until 24 to 48 hours after surgery, followed by aspirin (100 mg), clopidogrel (75 mg), and oral quaque die. Delayed application of antiplatelet drugs means that 24 to 48 hours after surgery, when the condition is stable, as indicated by CT review, aspirin (100 mg) + clopidogrel (75 mg), and oral quaque die will be administered.

The ECASES assessor, a nonsurgical participant, will evaluate each subject (study or control group) according to the ECASES scoring rules (see below) and make ECASES treatment recommendations to the protocol decision maker; the surgeon and their assistant will evaluate and discuss each subject (study or control group) based on their experience and make treatment recommendations to the protocol decision maker. The ECASES assessor and surgical participants will be unaware of their respective treatment recommendations, and the decision maker will select a treatment plan based on subject grouping (ECASES recommendations for the study group/operator’s experience for the control group) and inform the operators of the finalized treatment plan for the next operation; however, they will not inform the operator of the source of the regimen (derived from the ECASES system or operator’s experience) and the subject subgroup.

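### The trial is called double-blind, but any final plan that differs from the operators' own recommendation tells them the patient is in the ECASES arm

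*Protocol article*

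**What the plan says.** Section 2.3 of the protocol article states: "The study will be double-blind, blinded to the patient and investigator". It extends this over the whole trial: "neither the patients nor investigators will know the subject grouping throughout treatment and follow-up". The double-blind label also stands in the Abstract (Discussion paragraph), the Introduction, section 2.1 and the closing Discussion.

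Section 2.5 describes how the plan is set, in three steps:

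- For each subject in either group, the surgeon and assistant form a view "based on their experience and make treatment recommendations to the protocol decision maker". A non-operating assessor separately submits the ECASES recommendation. Neither side sees the other's.
- Then "the decision maker will select a treatment plan based on subject grouping": the ECASES recommendation in the study group, the operators' own in the control group.
- The decision maker must then "inform the operators of the finalized treatment plan for the next operation", but "they will not inform the operator of the source of the regimen" and does not disclose the group.

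Section 2.4 confirms that the operating team carries out the plan it is given. The closing Discussion relies on the withheld source as a protection against confounding and bias.

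**The concern.** The operators know which plan they submitted and learn which plan they must perform. Withholding the source protects them only if they cannot compare the two, and nothing in the design prevents the comparison. The three options in section 2.5 (stent with immediate antiplatelet drugs, stent with delayed antiplatelet drugs, no stent) are plainly distinguishable to whoever performs them.

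The surgeon and assistant are investigators in the ordinary sense, so the promise in section 2.3 cannot be kept for them. The leak is not spread evenly. It falls on the patients in whom the two strategies differ, who carry the whole treatment contrast. An operator who has been overruled could be influenced in either direction in later care or in the decision to order unscheduled imaging. If such an operator also rated outcomes, the mRS, which involves judgement, could be affected. Readers who see the label would credit the trial with a safeguard that it lacks.

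**Working it through.** The plan gives no figure on this point, so there is none to reproduce. The check applies Bayes' rule to the selection rule.

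**Inputs**

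- Allocation is 1:1 with 101 patients per arm (section 2.2), so the prior probability of the study arm is 0.5.
- The final plan is the ECASES recommendation in the study arm and the operators' recommendation in the control arm (section 2.5).
- d is the share of patients in whom the two recommendations differ. The article does not give it. Values of 10%, 30% and 50% are assumptions, chosen only to show a range.

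**Step 1: the final plan differs from the operators' plan.** P(differs | control) = 0, because control patients always receive the operators' plan. P(differs | study) = d. Hence

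P(study | differs) = 0.5d / (0.5d + 0.5 × 0) = 1 for any d > 0.

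This result needs no value for d.

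**Step 2: the final plan matches.** P(matches | control) = 1 and P(matches | study) = 1 − d. Hence

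P(control | matches) = 0.5 / (0.5 + 0.5(1 − d)) = 1 / (2 − d).

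**Step 3: size.** The expected number of study-arm patients unmasked with certainty is 101 × d. An operator who guesses study on a mismatch and control on a match is right with probability 0.5d + 0.5 = (1 + d)/2. Effective masking would give 50%.

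| Assumed d | Study patients unmasked, of 101 | P(control given match) | Correct guesses |
|---|---|---|---|
| 10% | 101 × 0.10 = 10.1 | 1/1.90 = 0.526 | 55% |
| 30% | 101 × 0.30 = 30.3 | 1/1.70 = 0.588 | 65% |
| 50% | 101 × 0.50 = 50.5 | 1/1.50 = 0.667 | 75% |

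A simulation of 200,000 patients at each of these three values agreed: no control patient appeared among the mismatches.

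**Step 4: can a small d rescue the claim?** Only at d = 0 is there no leak, and then both arms are treated identically and the trial compares nothing.

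**The case against.** Several points on the other side stand.

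- **Patients.** This mechanism reveals the arm to the surgeon and assistant, not to the patient. It does not show that patient masking fails.
- **Raters.** A reader might infer that the operators will score the 90-day mRS and NIHSS. The article does not say so. Section 2.7 names no rater, and a condensed article may leave that to the full protocol. The sentence "NIHSS and mRS scores will be used as tools for neurological function evaluation and completed by senior physicians" stands under preoperative evaluation and says nothing about follow-up. Equally, the CT reading panel in section 2.8 appears only inside a hemorrhage definition in a paragraph that refers to ECASS II. It does not establish that this trial has such a panel, either as a safeguard or as a resource.
- **Timing.** The operators learn the final plan after they have submitted theirs, so for that patient the leak cannot bias the recommendation or the choice of plan.
- **Limited discretion.** The antiplatelet regimen follows from the selected option. Section 2.7 schedules CT, MRI and vascular imaging for all patients, so unscheduled scans are only additional. Both facts limit the scope for bias without removing it.
- **Size.** A reader might take 30 to 50 unmasked patients as an estimate. The documents give no basis for any discordance rate, and 10% would give about 10.

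None of this answers the central point. The operators are investigators, and the procedure in section 2.5 discloses the allocation to them whenever they are overruled.

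**Conclusion.** The point holds as a contradiction between sections 2.3 and 2.5. Operator masking fails with certainty in every study-arm patient whose ECASES plan differs from the operators' plan. In patients whose plans match it weakens only moderately, to a probability of control between 0.526 and 0.667 over the assumed range. The certainty result rests only on the decision maker following the stated rule and on the operators remembering their own recommendation. The counts of about 10, 30 and 50 of 101 rest on assumed discordance.

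The stronger reading, that blinding fails altogether or that the primary outcome will be rated by unmasked operators, is not supported. The article shows neither a failure of patient masking nor who the postoperative raters are. The design remains usable. The label and the Discussion's claim about bias are wrong as written and should be corrected.

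**What to change.** 1. In the Abstract, the Introduction, sections 2.1 and 2.3 and the closing Discussion, replace double-blind with: *patient-blinded, with blinded outcome assessment; operators not reliably blinded*. Restrict the promise in section 2.3 accordingly.
2. Qualify the Discussion's statement that withholding the source minimizes bias: it does not conceal the arm from operators whose plan is overruled.
3. State in section 2.7 that the surgeon and assistant, and anyone who took part in that patient's plan discussion, do not score the postoperative NIHSS or mRS (above all the 90-day primary outcome) and do not read the outcome imaging. Raters should see neither recommendation. The words on blinded outcome assessment in item 1 are justified only with this rule in place. If the full protocol already contains it, a sentence saying so is enough.
4. Acknowledge as a limitation that operators may still influence later care and unscheduled imaging. The changes above do not remove this.

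The cost is a weaker blinding claim, some rewording and some rostering among existing staff. The article does not show how many suitable raters are available, so the sponsor should confirm this. Treatment, sample size and visits are unchanged.
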